# Effectiveness of Metformin Prolonged-Release Formulation on Achievement of Optimal Glycemic Control in Gestational Diabetes Mellitus: Protocol for a Pilot, Randomized, Double-Blind, Clinical Trial

**DOI:** 10.2196/79855

**Published:** 2025-12-19

**Keywords:** gestational diabetes mellitus, metformin, prolonged-release formulation, glycemic control, effectiveness

## Abstract

**Background:**

Gestational diabetes mellitus (GDM) is one of the most common complications in pregnancy. Optimal glycemic control is key to reducing the risk of adverse pregnancy outcomes. If glycemic control is inadequate, additional medications are needed. A large body of evidence has shown that metformin is an effective medication for GDM. Compared to the immediate-release formulation, the prolonged-release (PR) formulation of metformin offers some advantages with a single daily dose and has less frequent side effects, leading to better compliance. To date, no study has specifically reported the effectiveness of metformin PR in the treatment of GDM or the time required to achieve glycemic control after treatment. The results will help clinicians plan a better choice of treatment and follow-up for women with GDM and inadequate glycemic control.

**Objective:**

This study aims to evaluate the effectiveness of metformin PR in the treatment of GDM in terms of achieving glycemic control within 6 weeks, time to achieve glycemic control, and associated factors.

**Methods:**

A randomized, double-blind, placebo-controlled clinical trial will be conducted among 80 pregnant women diagnosed with GDM who had inadequate glycemic control at a university hospital in Thailand. The women will be randomized into 2 equal groups, receiving either metformin PR or a placebo in addition to nutritional therapy and behavioral modification. Dosage adjustment will be made every 2 weeks. If the glycemic target is not achieved within 6 weeks, insulin therapy will be initiated. All the participants and the investigators are blinded to the treatment provided. The primary outcome is the rate of achievement of glycemic control, and secondary outcomes are time to achieve glycemic control, rate of insulin therapy, and factors associated with the success of metformin PR use.

**Results:**

The study was funded in May 2025 when recruitment started. The study is projected to be completed in October 2026. Women with GDM who experienced inadequate glycemic control by nutritional therapy were assessed for eligibility. As of October 2025, 24 women with GDM agreed to participate and follow-ups were scheduled. The results are expected to be published in 2027.

**Conclusions:**

The results of this study will provide additional information on the use of metformin in the treatment of GDM, including the use of different formulations, rate of glycemic control, time to achieve glycemic control, and associated factors. This will help physicians better plan care for pregnant women with GDM, especially when glycemic control is inadequate, including choices of metformin formulation and dosage, follow-up schedule, and identification of women at risk of treatment failure.

**Trial Registration:**

Thai Clinical Trial Registry TCTR20250525007; https://www.thaiclinicaltrials.org/show/TCTR20250525007

**International Registered Report Identifier (IRRID):**

DERR1-10.2196/79855

## Introduction

Gestational diabetes mellitus (GDM) is one of the most common complications in pregnancy; it can lead to various adverse maternal and neonatal outcomes, including preeclampsia, cesarean section, large-for-gestational-age infants, macrosomia, birth injuries, shoulder dystocia, and neonatal hypoglycemia [1-3]. Optimal glycemic control (fasting plasma glucose [FPG] of <95 mg/dL and 2-h postprandial glucose, 2-h PPG of <120 mg/dL) is key to reducing the risk of developing adverse pregnancy outcomes [1-3].

In general, nutritional therapy, behavioral modification (including physical activity and exercise), and glucose monitoring and control are the main interventions to provide to all women with GDM to achieve glycemic targets. However, if glycemic control is inadequate, additional medications are needed. Insulin has long been used as the first-line medication in GDM. Nevertheless, a large body of evidence has consistently shown that metformin is also an effective medication for glycemic control in GDM. It has been reported that metformin helps in better glycemic control, better control of weight gain, reduction in adverse pregnancy outcomes, and reduction in insulin need and dosage requirement [4-14]. In addition, metformin has been reported to be safe to use during pregnancy [6,15-19] and appears to be more cost-effective compared to insulin in the treatment of GDM [20]. Currently, many international authorities recommend the use of metformin in women with GDM [1,21,22].

Different formulations of metformin are available, including an immediate-release (IR) formulation, with a time to maximum concentration of 3 to 4 hours and a 12-hour duration of action, and a prolonged-release (PR) formulation, with a time to maximum concentration of 7 to 8 hours and a 24-hour duration of action. Although both formulations have comparable effectiveness, metformin PR has advantages over its IR counterpart in terms of once-daily dosage with minimal gastrointestinal side effects, which helps improve compliance [23-28]. Gastrointestinal side effects have been reported with the use of metformin IR in previous studies, and some participants needed to stop the medication or reduce the dosage [4]. In another study, the use of metformin IR resulted in nausea and vomiting in 36% and 25% of the participants, respectively [5]. Therefore, metformin PR would be more suitable to use during pregnancy, not only because many pregnant women usually experience gastrointestinal symptoms, such as nausea and vomiting, but also because the medication has fewer side effects. Furthermore, with its once-daily dosage, compliance with the treatment will improve.

Although the benefits of metformin PR on diabetes have been reported, information on its potential benefits for the treatment of GDM is lacking. To address this knowledge gap, we will conduct a study to evaluate the effectiveness and associated characteristics of metformin PR in the treatment of GDM. The results will provide more insights into the use of metformin PR for the treatment of GDM. Understanding its effectiveness, time to achieve glycemic control, and the risk for treatment failure can help caring physicians make better decisions on treatment initiation, follow-up schedule for glycemic control evaluation, and identify those who are at higher risk for treatment failure. The results would be helpful in developing a higher quality of care for patients with GDM in the future.

Our hypothesis is that metformin PR is effective in GDM treatment in terms of the rate of adequate glycemic control and time to achieve glycemic target compared to nutritional therapy. Therefore, the primary objective of this study is to compare the rate of optimal glycemic control within 6 weeks between women with GDM who receive metformin PR and women who receive a placebo, in addition to standard nutritional therapy. The secondary objectives are to compare the time required to achieve optimal glycemic control and the rate of insulin therapy between the 2 groups, and to determine factors associated with the success of metformin PR treatment, such as prepregnancy BMI, degree of abnormalities of test results at the time of diagnosis, GDM risk factors, and other baseline characteristics.

## Methods

### Study Design

The study is designed as a randomized, double-blind, placebo-controlled trial and registered at the Thai Clinical Trial Registry (TCTR20250525007). Eligible participants will be randomly assigned in a 1:1 ratio to receive either metformin PR or a placebo. Each participant will be followed up every 2 weeks for glycemic control evaluation and dosage adjustment for 6 weeks.

According to the institutional practice guidelines, every woman with GDM will receive counseling by certified diabetes educator nurses and will be scheduled for follow-up every 2 weeks for glycemic control evaluation. If the glycemic target is not achieved after 6 weeks of intensive nutritional therapy, additional pharmacological treatment will be initiated. Therefore, this study will evaluate the primary outcome of glycemic control at 6 weeks after randomization.

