### GDM Diagnosis and Management

According to current institutional guidelines, GDM screening and diagnosis are offered to all pregnant women at the first antenatal care visit and repeated at 24 to 28 weeks of gestation if the initial screening results are normal. A 50-g glucose challenge test is used as a screening test with a 140 mg/dL cutoff value, and a 100-g oral glucose tolerance test is used for diagnosis using the Carpenter and Coustan criteria (≥2 abnormal values of 95, 180, 155, 140 mg/dL at 0, 1, 2, and 3 h). The current prevalence of GDM in the institution is approximately 15% to 20% of pregnant women.

After diagnosis, nutritional counseling and knowledge on behavioral modification are provided by certified diabetes educators. A glucometer is encouraged and offered for self-monitoring blood glucose (SMBG), but its use is based on women’s preference. FPG or 2-hour PPG, or both, are used for evaluation of glycemic control during follow-up. Glycemic targets are set at FPG <95 mg/dL and 2-hour PPG <120 mg/dL in >80% of the total SMBG test results.

If glycemic targets are not met at any time during pregnancy, repeat nutritional and behavioral counseling is offered. The women are reevaluated every 1 to 2 weeks. If adequate glycemic control is still not achieved within 4 weeks, pharmacological treatment will be initiated. In addition to insulin therapy, metformin will be offered as an alternative medication. The decision on choices of pharmacological therapy is based on the physician’s discretion and the woman’s preference.

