### Interventions

After initial screening and acquiring informed consent, the women will be randomly assigned to 2 groups—the intervention group or the control group.

For the intervention group, metformin PR will be provided to the participants, starting with 750 mg daily (1 tablet of metformin PR 750 mg). Follow-up is scheduled every 2 weeks for 6 weeks. Dosage adjustment will be made at each visit, depending on the results of glycemic control in a step-up protocol, that is, 750, 1000, 1500, and 2000 mg. The maximum dosage of metformin PR is 2000 mg per day. For dosage adjustment, 1 tablet of metformin PR 1000 mg will be used for a dosage of 1000 mg per day, 2 tablets of metformin PR 750 mg will be used for a dosage of 1500 mg per day, and 2 tablets of metformin PR 1000 mg will be used for a dosage of 2000 mg per day.

Pregnant women who are in the control group will receive 1 tablet of a placebo and will be scheduled for follow-up every 2 weeks for 6 weeks.

In addition to standard antenatal care according to institutional guidelines, pregnant women in both groups will receive individualized counseling on nutrition and behavioral modifications for glycemic control at every follow-up visit.

All participants are encouraged to adhere to the medication provided. A specific phone number will be provided to participants to receive an answer if they have any questions about the medications. Participants will be contacted every 2 days via a telephone call, SMS, or other online platforms to ensure medication adherence. Pill count will be performed at every visit, and additional encouragement will be provided. All participants are advised to avoid using other antidiabetic medications and other herbal products during the study period.

At the end of the study period of 6 weeks, glycemic control will be evaluated thoroughly, and appropriate treatment will be provided. Either the previous treatment will be continued or a new treatment will be initiated, after consultation with an endocrinologist, as appropriate. Standard antenatal care will also be provided until delivery. Treatment failure is defined as inadequate glycemic control after 2000 mg of metformin PR. In such a situation, insulin therapy is initiated.

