### Outcomes

The primary outcome of this study is the rate of achievement of optimal glycemic control within 6 weeks, which is defined as FPG <95 mg/dL or 2-hour PPG <120 mg/dL in >80% of total SMBG test results.

The secondary outcomes include time to achievement of optimal glycemic control, rate of insulin therapy, and rate of side effects. Treatment failure is defined as inadequate glycemic control after 2000 mg of metformin PR. In this situation, insulin therapy is initiated. Side effects will be evaluated by interviewing the participants at each visit and by additional contact via a telephone call, SMS, or other online platforms.

The participant timeline is displayed in Figure 1.

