### Data Collection and Management

Data will be collected at enrollment and at every visit. Data will be entered into the electronic case record form, including baseline and obstetric characteristics, such as age, parity, and prepregnancy BMI. GDM diagnosis and management data, such as gestational age at diagnosis, results of the 50-g glucose challenge test and 100-g oral glucose tolerance test, and glycated hemoglobin, will be collected. Glycemic control data, including FPG and 2-hour PPG at every visit, or percentage of abnormal SMBG test results, will also be noted. Furthermore, the time to achieve the glycemic target will be evaluated, as will side effects, such as bloating, nausea, and vomiting.

Data at every time point will be checked for completeness and entered into the electronic case record form using an electronic data capture system. Data range and values will be rechecked by another research assistant. Incomplete and invalid data will be rechecked with those in the case record form or medical record. An audit trail will be used to track and identify all actions performed on the data, ensuring data integrity.

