### Statistical Methods

Descriptive statistics, including number, percentage, mean, and SD, will be used to describe variables as appropriate. Comparisons of variables between groups will be made using the 2-tailed Student *t* test for continuous variables, such as age, BMI, and gestational age, or the chi-square test for categorical variables, such as parity and GDM risk factors. Comparison of rates of achievement of optimal glycemic control between groups will be performed using the chi-square test. Relative risks and 95% CIs will be evaluated. Time to achieve glycemic control will be compared between groups, using the Student *t* test or Mann-Whitney *U* test, depending on the distribution of the variables. Kaplan Meier curves will be used to estimate the survival curve of time to achieve glycemic control after treatment, and the log-rank test will be used to compare the survival curves between treatment and control groups. Rates of insulin therapy and side effects will be compared using appropriate statistical tests. Missing values will be handled using multiple imputation methods, as appropriate. Subgroup analysis by BMI categories, parity, or GDM risks will be performed as appropriate. All analyses will be performed on an intention-to-treat basis. A *P* value of <.05 is considered to indicate statistical significance.

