## Discussion

### Anticipated Findings and Importance

Although the effectiveness of metformin in the treatment of GDM has been demonstrated in previous studies, only metformin IR has been investigated [4-14]. No study has specifically reported the effectiveness of metformin PR, which could have advantages over metformin IR in terms of fewer side effects and a once-daily dosage that results in better compliance [23-28]. Moreover, no previous study has reported the time required to achieve glycemic control after metformin treatment.

Therefore, the results of this study will add additional information to the medical community. It can help caring physicians to make better decisions regarding the selection of appropriate dosage and formulation of metformin, as well as a follow-up schedule for evaluation of glycemic control. In addition, the results could also help identify women at a higher risk for unsuccessful glycemic control after metformin therapy.

Some challenges in conducting the study might include adherence to the scheduled treatment and follow-up. Various measures are planned to improve both important issues. All participants will be informed regarding the importance of adherence to the treatment and follow-up to achieve glycemic control. Participants will be regularly contacted every 2 days via a telephone call, SMS, or other online platforms to encourage adherence to the provided medications and follow-up schedule, and for the evaluation of any adverse events.

The results will provide more insights into the use of metformin PR for the treatment of GDM. Understanding its effectiveness, time to achieve glycemic control, as well as the risk for treatment failure, can help caring physicians make better decisions on treatment initiation and follow-up schedule for glycemic control evaluation, and identify those who are at higher risk for treatment failure. All the information would be helpful in developing a higher quality of care for patients with GDM in the future.

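### Time to glycemic control is seen only at weeks 2, 4 and 6 but analyzed as a continuous time, so the reported mean and median will be late

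*Protocol article*

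**What the plan says.** Outcomes in the protocol article makes the time an endpoint in its own right: "The secondary outcomes include time to achievement of optimal glycemic control, rate of insulin therapy, and rate of side effects". Study Design sets when control is assessed: "Each participant will be followed up every 2 weeks for glycemic control evaluation and dosage adjustment for 6 weeks". Interventions repeats that schedule.

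Data Collection and Management ties data capture to those visits: "Data will be collected at enrollment and at every visit". It describes the glycemic data as follows: "Glycemic control data, including FPG and 2-hour PPG at every visit, or percentage of abnormal SMBG test results, will also be noted". Home readings will not exist for everyone, because GDM Diagnosis and Management says: "A glucometer is encouraged and offered for self-monitoring blood glucose (SMBG), but its use is based on women’s preference". There is also contact between visits, but Interventions gives it another purpose: "Participants will be contacted every 2 days via a telephone call, SMS, or other online platforms to ensure medication adherence". Adverse Event Reporting and Harms adds adverse events to these contacts. Neither section mentions glucose readings.

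Statistical Methods compares the time between arms by t test or Mann-Whitney U, and adds: "Kaplan Meier curves will be used to estimate the survival curve of time to achieve glycemic control after treatment". A log-rank test accompanies the curves. Nothing is said about grouped or interval-censored times.

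Anticipated Findings and Importance claims novelty for the time itself: "Moreover, no previous study has reported the time required to achieve glycemic control after metformin treatment". That section, the Introduction and the Conclusions of the Abstract all say that the results will help clinicians plan the follow-up schedule.

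**The concern.** A woman who reaches target between two visits is recorded as controlled at the later one. Recorded times are therefore never early, and can be up to 14 days late if control lasts until the visit. Three post-baseline assessments leave three nominal values, 2, 4 and 6 weeks, plus not achieved. A mean or median of such values mixes the biology with the calendar, and the median can only land on a visit week.

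What is at stake is the absolute time. A statement such as control being reached in a median of 4 weeks would be new information offered to clinicians for planning follow-up. It would be late by an amount the trial cannot measure. Strengths and Limitations discusses the 6-week horizon but not the 2-week resolution.

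**Working it through.** **Inputs from the article.** Assessments at nominal weeks 2, 4 and 6 (Study Design). Achievement within 6 weeks of 95% on metformin PR and 70% on placebo; 40 per arm with 20% loss (sample size paragraph after Figure 1).

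**The plan's own figure.** The article gives none for time to control. Its one calculated figure, 40 per arm, is reproduced by the arcsine formula with two-sided 5% and 80% power. There h = 2·asin(√0.95) − 2·asin(√0.70) = 0.708, and n = 2 × (1.960 + 0.842)² / 0.708² = 31.3, rounded up to 32. Then 32 / 0.8 = 40. It is not in dispute here; it supplies the 32 evaluable women per arm used below.

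**Assumptions made here, not in the article.** Times follow a Weibull curve scaled to the plan's 6-week rate p, with shape k = 1 (constant rate), 1.5 or 2 (rate rising over time). Control, once reached, lasts to the next visit. Visits fall on their nominal dates.

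**Formulas.**
- Proportion controlled by week t: F(t) = 1 − (1 − p)^((t/6)^k).
- True median: 6 × [ln 2 / −ln(1 − p)]^(1/k).
- Visit-grid median: the first of weeks 2, 4 and 6 at which F reaches 50%.
- Visit-grid mean among achievers: [2·F(2) + 4·(F(4) − F(2)) + 6·(F(6) − F(4))] / F(6).
- True mean among achievers: for k = 1, 1/h − 6(1 − p)/p with h = −ln(1 − p)/6; for other k, numerical integration.

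**Worked case, metformin PR, k = 1.** h = −ln(0.05)/6 = 0.499 per week. F(2) = 1 − 0.05^(1/3) = 63.2%. True median 0.693/0.499 = 1.39 weeks; visit-grid median 2. True mean 1/0.499 − 6 × 0.05/0.95 = 1.69 weeks. Visit-grid mean (2 × 0.632 + 4 × 0.233 + 6 × 0.086)/0.95 = 2.85 weeks.

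**All cases (weeks).**

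| Shape | Arm | Recorded at week 2 | Median: true / grid / delay | Mean: true / grid / delay |
|---|---|---|---|---|
| 1 | Metformin PR | 63.2% | 1.39 / 2 / 0.61 | 1.69 / 2.85 / 1.16 |
| 1 | Placebo | 33.1% | 3.45 / 4 / 0.55 | 2.41 / 3.48 / 1.07 |
| 1.5 | Metformin PR | 43.8% | 2.26 / 4 / 1.74 | 2.36 / 3.38 / 1.02 |
| 1.5 | Placebo | 20.7% | 4.15 / 6 / 1.85 | 3.06 / 4.04 / 0.98 |
| 2 | Metformin PR | 28.3% | 2.89 / 4 / 1.11 | 2.87 / 3.85 / 0.98 |
| 2 | Placebo | 12.5% | 4.55 / 6 / 1.45 | 3.52 / 4.46 / 0.94 |

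Medians are 0.55 to 1.85 weeks late, and means among achievers 0.94 to 1.16 weeks late.

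**Effect on the comparison of arms.** The delay is nearly common to both arms. For k = 1, the difference in medians is 3.45 − 1.39 = 2.06 weeks true and 4 − 2 = 2 on the grid. The difference in means is 2.41 − 1.69 = 0.72 true and 3.48 − 2.85 = 0.63 on the grid. A simulation of the log-rank test (k = 1, 32 per arm, 3000 runs) gave power of about 0.91 with exact times and 0.90 with grouped times.

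**What the grid does estimate correctly.** At weeks 2, 4 and 6 themselves, the proportion already at target needs no assumption about when within the interval control began. Only statements about time between visits do.

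**The case against.** The strongest reply is that the stated secondary objective is to compare time between arms, and that comparison survives. Both arms share one schedule, the log-rank test remains valid with almost no loss of power, and the between-arm differences barely move. Kaplan-Meier curves on visit-documented events are common practice. All of this stands, and it confines the point to the absolute time.

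A second reply is that the list of glycemic data is open-ended, that the next sentence lists time to target as something to be evaluated, and that a full protocol or case record form may hold dated readings. That is possible, and a sentence saying so would settle part of the matter. But the article ties data collection to visits, names a percentage rather than a series, and makes meters optional, so at least some women would have only visit values.

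Three stronger readings are tempting and not supported:
- A reader might infer that the trial claims to inform follow-up at intervals shorter than 2 weeks. No section says this; the article speaks only of the follow-up schedule in general. Proportions at weeks 2, 4 and 6 do inform a schedule at that resolution.
- A reader might infer that, on the plan's own rates, most metformin PR responders reach control before week 2. The plan gives 6-week rates only. The 63% needs a constant rate; shapes 1.5 and 2 give 44% and 28%.
- A reader might take 2, 4 and 6 weeks literally. These are nominal; actual visit dates will scatter by some days.

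**Conclusion.** The point holds for the absolute time to control and no further. Followed as written, the plan would report medians roughly 0.55 to 1.85 weeks late and means among achievers roughly 0.9 to 1.2 weeks late, in a 6-week window. Between 28% and 63% of metformin PR women would be recorded at exactly week 2. These sizes rest on assumed Weibull shapes of 1 to 2 scaled to the plan's 95% and 70%, on control persisting to the next visit, and on nominal visit dates. The direction rests on the visit schedule alone.

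The primary outcome is untouched, and so is the sample size, which was computed for it. The log-rank comparison is essentially unaffected; its power was simulated for the constant-rate case only. The correction is worth making because the time itself is presented as a new finding that will help plan follow-up.

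**What to change.** 1. In Statistical Methods, analyze time to control as interval-censored or as grouped (discrete) time. The log-rank comparison may stay.
2. Replace the t test or Mann-Whitney comparison of mean or median time with the cumulative proportion at target by weeks 2, 4 and 6 in each arm, with 95% CIs.
3. In Strengths and Limitations, state that the resolution is 2 weeks, so the trial cannot locate control within a visit interval.
4. Optionally, where women already use a meter, capture dated readings for a supplementary analysis with a prespecified window. This should not become the main analysis: meter use is by preference, so the precision of the date would depend on who chose a meter.

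The cost is minor analysis work and no single mean or median time in weeks to report. No visit is added and no treatment rule changes. Items 1 to 3 apply equally to the 24 women who had already agreed to participate; item 4 may not, since their dated readings are not assured.

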#### Blinding

All participants will be blinded to the treatment received. Placebos will be prepared by a pharmacist to resemble metformin PR in shape, size, and color. All caring obstetricians will be blinded to the treatment and make decisions on dosage adjustment or initiation of insulin therapy at their discretion. Glycemic control will be blindly assessed by the investigators without knowing the group to which the participants are assigned.

In case of withdrawal or termination of the study protocol, such as the occurrence of severe adverse events or noncompliance, the treatment will be unblinded. Further individualized management will be provided as appropriate. In addition, emergency unblinding will be performed if the participants need to be evaluated or treated for medical or obstetric conditions other than GDM.

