### Oversight and Monitoring

#### Safety Management

All participants will receive standard antenatal care at every visit by obstetricians. In addition to physical examination, obstetric examination will be performed, including evaluation of fetal growth and fetal heart rate activity, either by clinical or ultrasonographic examinations. Additional procedures will be provided as appropriate, such as electronic fetal monitoring, detailed ultrasonographic examination, etc.

Glycemic control will be evaluated by FPG and 2-hour PPG or percentage of abnormal SMBG test results. Individual nutritional and behavioral counseling will be provided, customized for each participant. According to institutional guidelines, participants with FPG ≥200 mg/dL or glycated hemoglobin ≥10% will be admitted for further evaluation and initiation of insulin therapy by an endocrinologist.

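### The primary outcome is set both at week 6 and within 6 weeks, its time-point rationale conflicts with the management section, and it has no rule for insulin started before week 6

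*Protocol article*

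**What the plan says.** **Time point.** Study Design: "Therefore, this study will evaluate the primary outcome of glycemic control at 6 weeks after randomization". Outcomes: "The primary outcome of this study is the rate of achievement of optimal glycemic control within 6 weeks". The Introduction gives the primary objective as to "compare the rate of optimal glycemic control within 6 weeks". The Abstract's objective, the sample-size paragraph after Figure 1 and the Conclusions also use *within*. Follow-up visits are every 2 weeks for 6 weeks.

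**Rationale for 6 weeks.** The opening word of the Study Design sentence ties the time point to the institutional guideline rule just before it: "If the glycemic target is not achieved after 6 weeks of intensive nutritional therapy, additional pharmacological treatment will be initiated". GDM Diagnosis and Management, also describing institutional practice, says: "If adequate glycemic control is still not achieved within 4 weeks, pharmacological treatment will be initiated".

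**Insulin.** The Abstract places it after the window: "If the glycemic target is not achieved within 6 weeks, insulin therapy will be initiated". Interventions and Outcomes link it to inadequate control after 2000 mg of metformin PR. Two other places allow it with no stated time limit. Under Blinding, obstetricians "make decisions on dosage adjustment or initiation of insulin therapy at their discretion". Under Safety Management, women with FPG of 200 mg/dL or more, or glycated hemoglobin of 10% or more, "will be admitted for further evaluation and initiation of insulin therapy by an endocrinologist".

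**Scoring.** The primary outcome in Outcomes is defined by glucose readings alone. Statistical Methods specifies intention to treat for all analyses.

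**The concern.** A primary outcome has to classify every woman in one way, fixed before anyone sees results. Here the two wordings disagree for any woman who reaches target and then loses it. The *ever* reading of *within* is a natural one, because the plan also treats first achievement as an event, analysed by Kaplan-Meier as time to control. If the choice stays open, it could be made, or appear to have been made, with the results in view.

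The reason given for the 6-week point is a rule that the same article states differently elsewhere. That rule also bears on how long women on placebo go without drug treatment.

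The outcome definition does not say what happens to a woman who starts insulin before week 6. Taken literally, if her readings then come into target she is a success for her assigned arm. The assumed failure rate is higher on placebo (30% against 5%), so scoring rescued women as successes would pull the two rates together.

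**Working it through.** **1. The plan's own figure.** Inputs from the sample-size paragraph: 95% v 70%, 80% power, 95% confidence (two-sided 5% assumed), 20% loss. With the arcsine formula:

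- h = 2·asin√0.95 − 2·asin√0.70 = 0.708
- n = 2(1.960 + 0.842)² / h² = 31.3, so 32 evaluable per arm
- 32 / 0.80 = 40 per arm

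The stated 40 is reproduced and is not in dispute. Its two rates are stated for control *within* 6 weeks.

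**2. The two wordings as endpoints.**

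| Pattern over visits | Within 6 weeks (ever) | At 6 weeks |
|---|---|---|
| In target at week 2 or 4, out at week 6 | success | failure |
| First in target at week 6 | success | success |
| Never in target | failure | failure |

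The first row is where they part. How many women fall there is not given. As an illustration, take three visits with an equicorrelated normal latent variable (assumed correlation 0.8 to 0.5). If 60% are in target at each visit, 75% to 83% are in target at least once. At 70% per visit, 83% to 90% are.

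**3. Effect of the wording on the difference.** Two models, both assumptions, start from 95% v 70% *within* and ask what status *at* week 6 would be, with exact power at 32 per arm:

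- Latent model solved backwards: 80.0% v 44.8% (correlation 0.5) or 88.3% v 54.9% (correlation 0.8). The difference grows to 35 or 33 points, and power is 86% or 87%.
- Retention model, where 5% to 20% of achievers in each arm lose control by week 6: 0.95 × 0.95 = 90.3% v 0.70 × 0.95 = 66.5%, down to 76% v 56%. The difference shrinks to 24 to 20 points, and power is 66% to 40%.

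The direction depends on the model.

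**4. The 4-week and 6-week rules.** Study Design counts 6 weeks of intensive nutritional therapy. The management section counts 4 weeks after a missed target and repeat counseling. The two clocks may start at different points, but the article does not say so. Women enter only after missing target following counseling. If the 4-week clock started at the first missed target and were applied in the trial, it would therefore run out by trial week 4 at the latest.

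**5. When insulin can start.** With one dose step per 2-weekly visit (750, 1000, 1500, 2000 mg), 2000 mg is reached only at week 6, so the scheduled route puts insulin after the window. The discretion under Blinding and the thresholds under Safety Management are the routes to earlier use. The treatment-failure definition does not cover these, and it has no placebo counterpart.

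**6. Size if early insulin is scored as success.** Let f be the share of failures in each arm who start insulin and reach target before week 6. The rates become 0.95 + 0.05f and 0.70 + 0.30f, and the difference becomes 0.25(1 − f). Exact power of the Pearson chi-square test at 32 per arm:

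| f (assumed) | Metformin PR | Placebo | Power |
|---|---|---|---|
| 0 | 95.0% | 70.0% | 81% |
| 0.10 | 95.5% | 73.0% | 76% |
| 0.20 | 96.0% | 76.0% | 70% |
| 1/3 | 96.7% | 80.0% | 61% |

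**The case against.** *Within* is the dominant wording, and the one sentence that says *at* can be read as naming when the outcome is assessed. This is fair, and it points to the least disruptive repair. It does not settle which endpoint is meant, because Interventions also describes a thorough evaluation of control at the end of the 6 weeks.

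The 4-week and 6-week statements may count from different starting points. That is possible, so the two are better called unreconciled than contradictory. The article leaves the reader to guess.

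A reader might infer that the plan deliberately counts control on added drug as success. No section says so. The scheduled pathway puts insulin after the window, and the rate of insulin therapy is a separate secondary outcome. What stands is narrower: earlier insulin is permitted, and a glucose-only definition under intention to treat has no rule for it. An article may leave detailed handling to the full protocol or analysis plan, but here the definition as written already yields a score for these women.

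The rescue shares have no basis in the article, and the schedule suggests that early insulin would be uncommon. This stands. At 10% the loss is about 5 points of power (81% to 76%).

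**Conclusion.** The point holds in three parts. First, the primary outcome is stated as two different endpoints, which leaves room for a choice after the data are seen. Second, the rationale for the 6-week point rests on a guideline rule that the management section gives as 4 weeks, and the two are not reconciled. Third, insulin before week 6 is possible and, under the literal definition, control reached on it would be scored as success for the assigned arm.

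The size of the third part is unknown. Power of 76%, 70% or 61% rests on assumed rescue shares of 10%, 20% or one third in each arm, on 32 evaluable women per arm, and on the 95% v 70% rates. It might also be inferred that *within* raises the placebo rate and so shrinks the difference. The documents do not support this: *within* can raise both arms, and the two models in the working give opposite directions. The case on the time point is ambiguity, not a shown loss of power.

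**What to change.** State one primary endpoint in the objectives, Study Design, Outcomes, sample-size paragraph and Conclusions before unblinding. Changing the Study Design sentence to *within 6 weeks* keeps the 95% v 70% basis of the sample size. If status at week 6 is chosen instead, the sample-size rates must be restated for that endpoint.

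Add one line on scoring. In the primary analysis, a woman who starts insulin or another added antihyperglycemic before she first meets the target counts as not having achieved control on assigned treatment. If status at week 6 is chosen, the cut-off is week 6.

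Reconcile the 4-week and 6-week statements in Study Design and GDM Diagnosis and Management, including the point from which each is counted, and restate the time-point rationale from the reconciled text. No view is taken on which clinical rule is right.

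The cost is protocol wording and a registry update. Success rates may read slightly lower. With 24 of 80 women reported as recruited, the change can still be made blind.
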